#### Urinary sodium and potassium

2.9.5.

A 24-h urine collection and a spot urine collection will be used to measure electrolytes at the second baseline visit and each follow-up clinic visit by ion-selective potentiometric methods and urine creatinine by a standardized enzymatic assay on the Vitros 5.1 platform (66). Collections with total volume < 450 mL/d or creatinine <10 mg/kg/d will be considered incomplete (67). Participants will be instructed in proper technique and provided with two 3 L wide-mouthed, labelled, screw-top plastic urine jugs along with a collection device (urinal or hat). Twenty-four-hour urine collections will start following first-morning void on the day prior to the study visit and end with inclusion of first morning void on the visit day, and the spot urine will be collected in-person at the visit. Urine volume will be measured using a graduated cylinder, with aliquots frozen at -80C prior to assay.

#### Heart disease and stroke risk scores

2.9.6.

For participants who have not experienced previous CHD or stroke events, the 10-year risk of incident CHD (68) or stroke will be estimated using prediction algorithms specific to AI/AN adults. Both risk scores were developed by the Strong Heart Study, a large prospective cohort study of CVD in AI/AN adults from three distinct geographic populations (including Oklahoma) (68). The scores are based on data collected during baseline and at each clinic visit (age, HTN medications, systolic BP, blood lipids, diabetes, smoking status, and albuminuria).

### Covariate measures

2.10.

#### Medications

2.10.1.

Participants will be instructed to bring all current medications (prescription, over the counter, and herbal or vitamin supplements) to each clinic visit. The site study coordinator will review and record each participant’s medications and will query the patient’s medical records. Current antihypertensive medications will be documented and coded using a protocol from an ongoing study of cerebrovascular disease among American Indians (69).

#### Smoking and alcohol use

2.10.2.

Tobacco and alcohol use at each clinic visit will be assessed with questions previously used in rural AI/AN populations (70). Smoking questions will distinguish current, past, and never smokers, including number of cigarettes smoked per day and age at initiation or cessation. Use of smokeless tobacco will not be assessed for this study. Alcohol consumption will be assessed with questions asking about frequency and type of current and past consumption of alcoholic beverages, after a standard definition and reference images for the equivalent of one alcoholic beverage is provided.

#### Comorbid conditions

2.10.3.

We will document prevalent diabetes, stroke, or CVD (congestive heart failure, myocardial infarction, or CHD) via patient self-report at the first baseline visit and medical chart abstraction. Urine micro- and macro-albuminuria will be categorized based on lab values where a participant’s albumin: creatine ratio is 30–299 mg/g or ≥ 300 mg/g, respectively (71).

#### Demographic and administrative

2.10.4.

Sex, age in years, completed education, current employment, and marital status will be collected at the first baseline visit. Documented administrative variables will include clinic site, study arm (control, intervention), and primary care provider (anonymous ID number, used only for statistical analysis).

### Monitoring

2.11.

The participants’ healthcare providers will be alerted that their patients are adopting an antihypertensive diet. In addition to monitoring provided by each participant’s primary healthcare provider, a Data Safety Monitoring Board (DSMB) will be organized to monitor the safety of all study participants. The DSMB will be responsible for safeguarding the interests of study participants, assessing the safety and efficacy of study procedures, ensuring data quality, and for monitoring the overall conduct of the study. The DSMB will be comprised of independent, doctorate-level professionals in the fields of medicine and AI/AN health. They will provide recommendations to the lead researcher, specifically related to starting, continuing, and stopping the study. In addition, the DSMB will be asked to provide recommendations, as appropriate, about: efficacy of the study intervention; benefit/risk ratio of procedures and participant burden; selection, recruitment, and retention of participants; adherence to protocol requirements; completeness, quality, and analysis of measurements; data and statistical analysis plan; amendments to the study protocol and consent forms; performance of individual study sites and core lab; adverse and serious adverse events; and participant safety. Meetings will be held once per year, with additional meetings or conference calls scheduled as needed. The lead researcher will promptly report all protocol deviations or unexpected, serious adverse events to the Washington State University Institutional Review Board and other relevant review boards, as per their protocols.

### Data analysis

2.12.

All data collected on-site will be scanned and uploaded to a secure server and entered into a REDCap database (72). Data will be reviewed by the biostatistician monthly to quickly identify data quality issues. For quality control, data from 10% of randomly selected participants will be entered twice. An intention-to-treat analysis will be used. Success of randomization will be assessed by using t-tests and chi-squared tests to compare baseline variables in the intervention and control groups. All inferential results will be presented as point estimates with 95% confidence intervals. Data analysis will be performed using Stata 14 (StataCorp LP, College Station TX, 2013).

Linear regression will be used to compare primary and secondary outcomes between the intervention and control groups at 8- or 12-week post-baseline assessments, with treatment group, baseline value, and study site as the independent variables. Since there may be differences between the study sites regarding availability of healthy food at local stores, an interaction term between intervention and site will be included. If the interaction is significant, all analyzes will be repeated after stratifying by site. Sensitivity analyzes will adjust for variables that appear unbalanced between groups at baseline. All 370 participants will be included in the analysis of data from the 8-week visit, but the 25 pilot study extended support (intervention group) participants will be excluded from analyzes involving data from the 12-week visit. Next, generalized estimating equations will be used to simultaneously assess outcome values measured at 8 and 12 weeks. To assess effectiveness of the extended support pilot study, a generalized estimating equation will be used to analyze data for all four time points (8 weeks, 12 weeks, 6 months, and 12 months), with independent indicators for each time point that do not impose a linear trend on the outcome. These models adjust standard error estimates to properly account for within-person correlation in the outcome values over time.

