#### Sample size

2.3.1.

Data from previous DASH interventions (51, 52) was used to estimate a sample size of 185 participants per group required to detect at least a 5.3 mmHg difference in mean systolic BP at 8 weeks, and a 5.7 mmHg difference in the 12-week analysis excluding the 25 extended support pilot study participants. Power of 80%, alpha error rate of 0.05, and a standard deviation of 18 mmHg based on previous 8- or 9-week trials were assumed.

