#### Recruitment

2.3.2.

A total of 370 participants will be recruited (approximately 120 from each site) with equal representation of men and women. At each clinic, separate lists of men and women in the target age range with physician-diagnosed HTN and at least two systolic readings ≥130 mmHg will be created. Each list will be randomly sequenced by the study biostatistician. Starting at the top of the lists, the research team will work with clinic staff to review medical charts for additional eligibility criteria. For patients who meet eligibility criteria, study staff will contact the primary care provider to secure approval for participation. Patients will be contacted by telephone and/or in-person at their next clinic visit to ascertain interest about the study and confirm eligibility. Eligible individuals will be scheduled for an initial baseline visit, ideally within 2 weeks of the in-person contact. Final determination of eligibility will occur at the second baseline visit based on an additional BP measure and compliance with study protocols (described below).

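### The primary regression includes a treatment-by-site interaction but does not say which contrast is the primary effect, while the trial is powered for the overall comparison

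*Protocol article*

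**What the plan says.** Section 2.12 (Data analysis) compares the arms at 8 or 12 weeks by linear regression, for primary and secondary outcomes alike. The regressors are treatment group, baseline value and site. Because access to healthy food may differ between sites, the section then adds: "an interaction term between intervention and site will be included. If the interaction is significant, all analyzes will be repeated after stratifying by site". It gives no significance level for the interaction, no step for a non-significant result, no coding for site, and no statement of which coefficient or contrast is the primary treatment effect.

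Section 2.3.1 (Sample size) gives "185 participants per group required to detect at least a 5.3 mmHg difference in mean systolic BP at 8 weeks". The assumptions are "Power of 80%, alpha error rate of 0.05, and a standard deviation of 18 mmHg", the last taken from earlier trials. Section 2.3.2 (Recruitment) plans 370 participants, "approximately 120 from each site", and section 2.2 (Setting) names three clinics.

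**The concern.** The sample size rests on one overall difference between two groups of 185. The model as written has three treatment effects, one per site, and the text does not say how they become one result. An analyst who fits it with default indicator coding and reads the line labelled treatment would be reporting the effect at whichever clinic was coded as the reference. That estimate is far less precise than the one the trial was sized for, and it changes with the choice of reference site. Other readings of the same fitted model give very different power. The primary estimate, confidence interval and p-value could therefore turn on a choice that the protocol leaves open.

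**Working it through.** **Inputs.** Difference 5.3 mmHg, SD 18 mmHg, alpha 0.05, power 80%, 185 per arm (section 2.3.1); 370 participants and three sites of about 120 (sections 2.2 and 2.3.2). Assumptions: two-sided test (not stated, but "All inferential results will be presented as point estimates with 95% confidence intervals" fits it), 1:1 allocation within site, and near-equal sites, so 370/6 = 61.7 per arm per site.

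**1. Reproduce the stated design.**
- n per arm = 2 × (18 × 2.80 / 5.3)² ≈ 181, or 182 with unrounded z values and rounding up; the protocol states 185.
- SE of the overall difference = 18 × √(2/185) = 1.87 mmHg.
- Power at 5.3 mmHg = Φ(5.3/1.87 − 1.96) = 80.8%.
- Detectable difference = 2.80 × 1.87 = 5.24 mmHg.

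The stated figures are reproduced as a plain two-group comparison.

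**2. What the interaction model contains.** With T for treatment, S2 and S3 as indicators for sites 2 and 3, and the baseline term left out for brevity:

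Y = β0 + β1·T + γ2·S2 + γ3·S3 + δ2·T·S2 + δ3·T·S3 + error.

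The treatment effect is β1 at site 1, β1 + δ2 at site 2 and β1 + δ3 at site 3. Under this coding, β1 is the effect at the reference site.

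**3. Precision of the reference-site coefficient.**
- SE = 18 × √(2/61.7) = 3.24 mmHg, which is √3 = 1.73 times 1.87. The design matrix for sites of 123, 123 and 124 gives 3.25.
- Power at 5.3 mmHg = Φ(5.3/3.24 − 1.96) = 37%.
- Detectable difference = 2.80 × 3.24 = 9.1 mmHg.
- 95% CI half-width = 1.96 × 3.24 = 6.4 mmHg, against 1.96 × 1.87 = 3.7 mmHg overall.

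The residual variance and baseline slope are still estimated from all 370 participants, but the treatment contrast comes from one clinic.

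**4. Precision of the site-averaged effect from the same model.** This is β1 + (δ2 + δ3)/3, the mean of three site effects. With equal sites its SE is 3.24/√3 = 1.87 mmHg and its power 80.8%, the same as the model without the interaction.

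**5. Joint test of all treatment terms (3 df)**, if the effect is the same at every site: noncentrality (370/4) × (5.3/18)² = 8.02, power about 65%.

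**6. Baseline adjustment.** The model adjusts for baseline, but the protocol does not say whether 18 mmHg is the SD before or after that adjustment. If before, the SD is multiplied by √(1 − r²), where r is the baseline-outcome correlation. The protocol gives no r, so a range is shown.

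| Assumed r | SE one site (mmHg) | SE overall (mmHg) | Power one site | Power overall |
|---|---|---|---|---|
| 0 | 3.25 | 1.87 | 37% | 81% |
| 0.3 | 3.10 | 1.79 | 40% | 84% |
| 0.5 | 2.81 | 1.62 | 47% | 90% |
| 0.7 | 2.32 | 1.34 | 63% | 98% |

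**7. Unequal sites (purely illustrative, 60/90/220; SD 18).** Reference-site power is 21% if the smallest site is the reference and 59% if the largest is. The equally weighted average has 69% power and the size-weighted average 81%.

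**The case against.** The strongest reply is that the text points to a whole-trial effect. It speaks of comparing the two arms, lists only three regressors before the interaction is mentioned, gives the interaction its own reason and one use, and includes all 370 participants at 8 weeks. Repeating analyses by site also presupposes an unstratified analysis to repeat. On this reading the interaction is a heterogeneity check, and coding and contrasts belong in a statistical analysis plan that is not shown.

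Much of this stands. A reader might infer that including the interaction in itself turns the primary result into one clinic's effect and cuts power to 37%. The documents do not support that. The loss needs two further steps, indicator coding of site and reporting that single coefficient as the trial result, and the article states neither. Step 4 shows that the same fitted model can deliver full power. The 37% is also only one scenario, as step 6 shows.

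What does not stand is that this is only omitted detail. The article states positively that the term is included, and the only consequence it attaches is the stratified repeat. Followed literally, the stated model yields no single effect that matches the powered comparison. An analysis plan that dropped the term would depart from this text; one that named an averaged contrast would supply what the text leaves open.

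**Conclusion.** The concern holds in conditional form. Section 2.12 specifies a model with a treatment-by-site interaction and does not fix the primary contrast; section 2.3.1 is sized for the overall effect. At SD 18 with near-equal sites, power for 5.3 mmHg is about 37% if the reference-site coefficient is read, about 65% for a joint test, and about 81% for the site-averaged effect. If 18 mmHg is the unadjusted SD and the baseline correlation is 0.3-0.7, the one-site figure is about 40-63% and the overall figure 84-98%, so the gap stays large. These figures assume a two-sided test, 1:1 allocation within site and, for the joint test, a common effect across sites. They do not show that the trial is underpowered or that a one-site coefficient will be reported.

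**What to change.** State in section 2.12 that the primary effect is the treatment coefficient from the model with treatment, baseline value and site only. Move the treatment-by-site interaction to a separate secondary model, tested on 2 df as a check of heterogeneity. If the interaction is to stay in the main model, name the site-averaged marginal effect as primary and give its weights, since weighting matters once sites differ in size. Reporting the three site-specific effects with confidence intervals whatever the interaction p-value is good practice, but optional.

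The cost is one or two sentences, with no new data and no change in sample size. The change should be made before outcome data are examined by arm.

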### Study aims

2.1.

The NOSH study aims are to: (1) evaluate the effect of the NOSH intervention on BP and secondary outcomes in urban AI/AN adults with HTN; and (2) conduct a pilot study after the intervention concludes to evaluate extended support from an RD for an additional 6 weeks among a subset of participants. NOSH is a randomized, wait-list control trial (Figure 1). After completion of the two baseline visits, participants will be randomized into either the intervention or waitlist control group. Waitlist control condition participants will receive a brochure about the benefits of a low-sodium diet and complete weekly phone calls to collect BP readings and place grocery orders. After completion of data collection (12-months post-baseline), participants will be offered the intervention. The intervention group will receive the intervention and groceries (described in 2.6). At week 8, if participants are interested in participating in the pilot study, they will be randomized into either the pilot study control or extended support (intervention) groups. It is hypothesized that NOSH will result in improved BP management and secondary outcomes compared to the control condition. For the extended support pilot study, it is hypothesized that BP will attenuate toward baseline in both groups of the pilot study, but extended support will lead to more sustained improvement. The study design used to address these aims is shown in Figure 1.

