#### Consent

2.3.4.

The in-person screening will take place at the first baseline visit, which will occur within 2 weeks of initial screening for eligibility and interest. A research assistant will describe the study and risks of participation. The site study coordinator will also review the study and measure BP. For people whose average BP is within eligibility limits, the site study coordinator will administer the full informed consent protocol, explaining study goals, procedures, and potential risks, in addition to requesting Health Insurance Portability and Accountability Act (HIPAA) authorization to allow ongoing access to their medical records (HIPAA is meant to protect a patient from having their information disclosed without the individual’s consent or knowledge). Clinic staff will enter information pertinent to the patient’s care in the medical record notes as it is deemed appropriate and will document provider approval to participate in the study. These notes will be left to the discretion of clinic staff and will not be shared with the study team. Participants will provide written informed consent and HIPAA authorization.

For the extended support pilot study, at the 8-week appointment, while intervention group participants are completing their follow up data collection, the research assistant will access the next assignment on a randomized list created by the study biostatistician. If intervention group participants are interested in participating in the pilot study, they will undergo an additional informed consent process and be further randomized to one of the following two groups: (1) pilot study control, or (2) extended support (pilot study intervention). Potential participants will be clearly informed that their choice whether to participate in the pilot study will not affect their participation in the 12-week follow-up for the main trial.

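### At 12 weeks the plan removes 25 week-8 volunteers from the intervention arm only, so that comparison is not intention-to-treat and will be biased if volunteers differ from non-volunteers

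*Protocol article*

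**What the plan says.** Section 2.12 (Data analysis) of the protocol article states: "An intention-to-treat analysis will be used". It puts all 370 participants in the 8-week analysis, then says that "the 25 pilot study extended support (intervention group) participants will be excluded from analyzes involving data from the 12-week visit". The regression adjusts for baseline value and site. A GEE on the 8- and 12-week values together follows.

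Section 2.1 (Study aims) gives the route into the pilot for intervention participants: "At week 8, if participants are interested in participating in the pilot study, they will be randomized" to pilot control or extended support. Section 2.3.4 (Consent) adds a separate consent and a randomised list. Section 2.6 (Intervention) places the extra dietitian calls in weeks 9 to 14, so they span the 12-week visit.

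Section 2.3.1 (Sample size) allows for the exclusion in the power calculation, quoting "a 5.7 mmHg difference in the 12-week analysis excluding the 25 extended support pilot study participants". The article describes no other allowance for it.

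**The concern.** Pilot entry happens after the main randomisation, is open to one arm only, and depends on attending week 8 and wanting more dietitian contact. Removing part of that group leaves an intervention arm with fewer volunteers than were randomised to it, set against an intact control arm. Baseline value and site need not capture willingness to continue, or response by week 8, either of which may be related to BP at week 12.

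What is at stake is the 12-week effect on the primary outcome. Section 2.8 schedules home systolic BP at 12 weeks, section 2.3.1 gives a detectable difference for it, and section 2.12 specifies no later comparison of intervention with control. It is the planned randomised evidence on whether the effect outlasts the 8-week programme. The joint GEE may also be affected, depending on how the exclusion is read.

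**Working it through.** **Inputs from the article.** 185 per group (370 in total); 25 removed, all from intervention, leaving 160 against 185; "Power of 80%, alpha error rate of 0.05, and a standard deviation of 18 mmHg". A two-sided alpha is assumed, because sidedness is not stated.

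**Assumed inputs.** The text gives neither the pilot allocation ratio nor the number of pilot controls, and Figure 1 is not shown. I take 1:1 (25 pilot controls), with a range for extended support to control of 2:1 (about 12 controls) to 1:2 (50 controls). D, the adjusted 12-week systolic BP difference between volunteers and non-volunteers, is unknown; I use 2, 5 and 10 mmHg. Follow-up is taken as complete.

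**Step 1: the plan's own figures.** For two means, n per group = 2 × (1.960 + 0.842)² × 18² / 5.3² = 182 after rounding up. The stated 185 reproduces within 3%, and 185 per group gives 80.8% power. The detectable difference is (1.960 + 0.842) × 18 × √(1/n₁ + 1/n₂):

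- 185 v 185: 5.24 mmHg
- 185 v 160: 5.44 mmHg

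The stated 5.7 mmHg at 12 weeks is therefore conservative for 185 v 160, where power at 5.7 is 83.5%.

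**Step 2: how far the exclusion changes the arm.** The intervention mean is the non-volunteer mean plus D times the volunteer share. The exclusion therefore shifts it by D × (share before − share after).

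| Assumed pilot (extended : control) | Share before | Share after | Multiplier | Shift for D = 2, 5, 10 mmHg |
|---|---|---|---|---|
| 2:1 (25 : 12) | 37/185 = 0.200 | 12/160 = 0.075 | 0.125 | 0.25, 0.62, 1.25 |
| 1:1 (25 : 25) | 50/185 = 0.270 | 25/160 = 0.156 | 0.114 | 0.23, 0.57, 1.14 |
| 1:2 (25 : 50) | 75/185 = 0.405 | 50/160 = 0.312 | 0.093 | 0.19, 0.46, 0.93 |

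If volunteers have the lower BP, the intervention mean rises and the effect is understated. If they have the higher BP, the effect is overstated. If D = 0 there is no bias.

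**Step 3: does weighting restore the arm?** Under 1:1, each pilot control gets weight 2 and everyone else weight 1. The weighted volunteer share is 50/185 again. Effective n = 185² / (135 × 1² + 25 × 2²) = 34,225 / 235 = 145.6. The detectable difference for 185 v 145.6 is 5.59 mmHg, with 81.6% power at 5.7. For 2:1 and 1:2 the effective n is 130.6 and 153.8, and the detectable difference 5.76 and 5.50 mmHg.

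**Step 4: simulation.** I ran 4,000 replicates per scenario with a 1:1 pilot, a true effect of −5.7 mmHg and regression on treatment and baseline.

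| D (mmHg) | Planned exclusion | Weighted |
|---|---|---|
| about 0 | −5.69 | −5.69 |
| about −4.6 | −5.20 | −5.72 |
| about −8.4 | −4.74 | −5.69 |
| about −12.8 | −4.25 | −5.70 |

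The planned analysis moves by about 0.114 × D, as step 2 predicts. In all three scenarios with non-zero D, volunteers were set to do better. That is a choice made for the check and not evidence about the trial.

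**Step 5: the GEE.** The exclusion covers any analysis that involves 12-week data. The joint model uses such data, so a literal reading removes all records of the 25, including 8-week values taken before extended support began. The GEE sentence itself states no exclusion, and the same section keeps all 370 for 8-week data. The text supports two analysis sets.

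**The case against.** The exclusion is deliberate, disclosed and counted in the power calculation. It also has a reason: the 25 receive further dietitian calls from week 9, and leaving them in would mix a second intervention into the effect of the 8-week programme. That reason stands, and the fix below also sets their 12-week values aside. What it does not justify is leaving the gap in the arm uncorrected while calling the analysis intention-to-treat.

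The bias is conditional and may be small. The article gives no value for D, and with SD 18 the standard error for 160 v 185 is 18 × √(1/160 + 1/185) = 1.94 mmHg, so a shift of 0.57 mmHg is about 0.3 standard errors. This stands and limits the weight of the point.

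Some stronger readings are tempting, but the article does not support them:

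- **The 25 are simply self-selected.** They are randomised from among volunteers, and the volunteers drawn as pilot controls stay in. That is why weighting can work.
- **The bias runs toward no effect.** Engaged responders may volunteer, but so may people still struggling at week 8.
- **The exclusion breaks an undertaking to participants.** Section 2.3.4 says that "their choice whether to participate in the pilot study will not affect their participation in the 12-week follow-up for the main trial". That concerns taking part in follow-up, not membership of an analysis set.
- **The GEE certainly loses the 8-week values.** That follows only from the literal reading.

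**Conclusion.** The point holds in a limited form. The declared intention-to-treat principle and the 12-week rule contradict each other: 25 participants leave one arm after randomisation, through a route that depends on volunteering at week 8, and adjustment for baseline value and site does not restore the arm. Bias follows only if volunteers differ from non-volunteers after that adjustment. Its direction is unknown, and its size is 0.09 to 0.125 times the difference over the assumed pilot ratios. That is modest against 5.7 mmHg unless the difference is large.

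A reader might infer that the trial's main result is compromised. It is not: the 8-week regression keeps all 370. The affected analyses are the 12-week comparison and, on the literal reading, the joint GEE. The arithmetic is secure given its inputs, but the pilot ratio and the volunteer differences are assumptions.

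**What to change.** Amend section 2.12 before the 12-week data are compared by arm:

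1. State the 12-week target as the effect of NOSH without extended support.
2. For that target, set aside only the 12-week values of the extended-support group. Weight each pilot control by the inverse of the actual probability of allocation to pilot control (2 if the pilot is 1:1), give everyone else weight 1, and use robust standard errors.
3. Keep all 370 participants' 8-week values in the joint GEE, and say so.
4. Report a 12-week analysis of all 370 as randomised as a sensitivity analysis, noting that 25 of them had extra support. Confine the intention-to-treat label to analyses that keep everyone as randomised.
5. Confirm that pilot consent is obtained before the pilot assignment is known. Section 2.3.4 describes the research assistant accessing the next assignment before it describes interest and consent. If consent could depend on the assignment, the weights are not valid.

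The cost is analysis wording and a little precision, with no new data. Under 1:1 the detectable difference goes from 5.44 mmHg unweighted to about 5.6 mmHg, inside the stated 5.7. Over the assumed ratios it is 5.50 to 5.76 mmHg, so a 2:1 pilot would put it slightly above 5.7.
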